### Participant recruitment

The study aims to recruit 350 participants across the three cohorts:

**“Extreme Visceral Pain”:** Participants reporting high pain despite low or no visible disease activity.**“Lack of Visceral Pain”:** Participants with active visceral disease but low pain levels.**“Healthy Controls”:** Individuals without any chronic visceral pain or relevant disease.

Participants with a diagnosed disease will be recruited from referrals through clinical advisors, and healthy control participant will be recruited through social media and public advertisements across Cambridge. All participants must be at least 18 years old, able to provide informed consent, and based in the UK. Healthy Controls will be age- and gender-matched with the other two cohorts. After assessing that the individuals can participate in the study and have given consent, each one will be placed in one of the three participant cohorts, and the assessments will be realised according to Fig 1. Eligible participants who have provided consent will be invited to undergo the following assessments:

**Fig 1 pone.0350169.g001:**
[figure not shown]
ADVANTAGE Study Protocol Overview Across All Three Cohorts. Comprehensive timeline showing assessment components and participant journey for Extreme Visceral Pain (high pain despite low disease activity), Lack of Visceral Pain (low pain despite high disease activity), and Healthy Controls cohorts. All participants complete baseline visit (~3 hours) with structured clinical interview, validated questionnaires (BPI-SF, McGill, disease-specific scales), quantitative sensory testing (QST: thermal, vibration, pressure pain thresholds), and ADVANTAGE Diary remote mobile app setup for daily pain ratings (0-10 Likert scale). Extreme Visceral Pain and Lack of Visceral Pain cohorts provide biological samples (50 mL blood for DNA/serum, urine, vaginal swabs, faeces). Extreme Visceral Pain and Healthy Controls proceed to 4-week wearable monitoring (chest-worn respiratory sensor, wrist-worn activity/HR sensor) followed by return visit (~1.5 hours) for repeat assessments, device return, and optional bio-sampling.

Remote mobile app to track pain intensityA first onsite visit, consisting of:Health screening through structured interviewQuestionnairesPhysical Examination, including quantitative sensory testingBio samples collection (not applicable for healthy controls)Training for wearable use (if applicable)Remote mobile app setup to track anxiety, and body position in addition to pain intensityFollow-up visit (for participants using wearable sensors only), consisting of:Repeat of procedures from the first onsite visit (sensory testing is optional)Return of wearable

Potential participants in the Extreme Visceral Pain and Lack of Visceral Pain cohorts will be identified by their clinical team based on the inclusion and exclusion criteria outlined in Table 1. Interested individuals can either contact the research team directly or give consent for their clinical team to share their details with researchers. After the initial contact by the clinical team, the research team will follow up to provide more information about the study and ask relevant screening questions, including a pain score if the participant does not have access to the remote mobile app.

**Table 1 pone.0350169.t001:** Inclusion and Exclusion Criteria for the Extreme Visceral Pain and Lack of Visceral Pain cohorts. Comprehensive eligibility matrix for the remote mobile app sub-study, wearable sensor sub-study, and bio-sampling sub-study. Common criteria: ≥ 18 years, UK-based, informed consent capable. Sub-study exclusions ensure safety (pacemakers, contact dermatitis), feasibility (travel restrictions), and cohort purity (no confounding pain conditions). Criteria support n = 350 total recruitment with n = 100 wearable sub-study power (80% power).

Sub-study	Inclusion Criteria	Exclusion Criteria
Remote mobile app	Pain, or lack of pain, associated with one or more of the specified visceral diseases or chronic pain conditions as diagnosed by an expert NHS medical professional.	Not able to fulfil the inclusion criteria
	Able to provide informed consent electronically	
	Aged 18 years and over	
	Living in the UK	
Wearable sensor	Able to fulfil the inclusion criteria of the remote mobile app sub-study	Unable to attend or visit the research site.*
		Travel abroad in the plan duration of wearable sub-study
	Have completed and adhered to the procedure in remote mobile app sub-study	
		Unable or unwilling to use body sensor for any reason (e.g. contact dermatitis over wear zone, implanted pacemaker or defibrillator, allergy or hypersensitivity to nickel)
Bio-sampling	Pain associated with one or more of specified visceral diseases or pain condition diagnosis by an NHS medical professional	Unable to attend or visit the research site.*
	Meet further clinical criteria for genetic sampling and analysis (see Supplementary Information)	
	Able to provide informed consent	Not able to fulfil the inclusion criteria
	Aged 18 years and over	
	Lives in the UK	

** Participants are eligible for the study regardless of their location, as long as they are willing and able to travel to the research site.*

To enable researchers outside of the clinical care team in the Cambridge site to contact individuals about research opportunities, we will use the existing “consent for contact” system. Through this system, individuals can indicate their interest in research studies via MyChart or an equivalent National Health Service (NHS) health record app, allowing researchers to identify, pre-screen, and contact eligible individuals. Study information will be shared with the potential participants through a Participant Information Sheet (PIS), either in print or electronically (see Supplementary Information for a PIS example).

Potential participants will then be screened and assessed for eligibility. All eligible participants will be offered the option to take part in the remote mobile app sub-study. Those who consent and complete the remote mobile app sub-study may be invited to the research site to join the wearable sub-study. Eligible participants will also be invited to participate in the bio-sampling sub-study.

The Healthy Controls cohort will go through a similar identification by the research team based on the inclusion and exclusion criteria outlined in Table 2. Participants in this cohort will be called to join the study if their demographics align with the current recruitment in the other cohorts by age and gender.

**Table 2 pone.0350169.t002:** Inclusion and Exclusion Criteria for the Healthy Controls cohorts. Comprehensive eligibility matrix for the remote mobile app sub-study, and wearable sensor sub-study. Common criteria: ≥ 18 years, UK-based, informed consent capable. Sub-study exclusions ensure safety (pacemakers, contact dermatitis), feasibility (travel restrictions), and cohort purity (no pain conditions).

Inclusion Criteria	Exclusion Criteria
Age over 18 years	Unable to attend or visit the research site *
	Inability to give full informed consent
	Self-reported pregnancy at the time of screening
Willing to complete pain diary and wearable sensor usage	Other neurological disease associated with gross structural or functional abnormalities of the central nervous system
	Any chronic pain condition
	Planned surgery within a month of screening
	Presence of pain or waiting for pain investigation
	Travel abroad in the plan duration of wearable usage
	Unable or unwilling to use body sensor for any reason (e.g., contact dermatitis over wear zone, implanted pacemaker or defibrillator, allergy or hypersensitivity to nickel)

** Participants are eligible for the study regardless of their location, as long as they are willing and able to travel to the research site.*

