### Bio-sampling

Participants from Extreme Visceral Pain and Lack of Visceral Pain cohorts will be asked to provide various samples to help researchers understand the similarities and differences in how conditions affect chronic visceral pain. Participants may choose to donate some samples while opting out of others, including those used in research involving non-human models.

**Whole blood:** Up to 50 mL of whole blood will be obtained through venepuncture. 5 mL of the whole blood sample will be sent for DNA extraction at the Department of Medical Genetics, University of Cambridge. 40 mL of the whole blood sample will be processed and sent for analysis and long-term storage to the Wolfson Sensory, Pain and Regeneration Centre at King’s College London. 5 mL of the whole blood sample will be processed and sent for long term storage to the Centre for Reproductive Health, Institute for Regeneration and Repair, University of Edinburgh.

**Urine:** Participants will collect mid-stream urine samples using a sterile device (UNI0054 or Colli-pee) at home or in the clinic, returning the samples via post. The urine sample will be sent to the Centre for Reproductive Health, Institute for Regeneration and Repair, University of Edinburgh.

**Vaginal swab:** Participants will self-collect a low vaginal swab (using BBLtm culture Swab MaxV or OMNIgene•vaginal | OMR-130), following provided instructions, and return the sample by post. The vaginal swab samples will be sent to the Centre for Reproductive Health, Institute for Regeneration and Repair, University of Edinburgh.

**Faeces:** Participants will collect up to three samples (using OMNIgene•GUT | OMR-200) at home and send them by post to the Cambridge Institute for Medical Research, University of Cambridge.

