### Key exploratory endpoint

The goal at the exploratory phase is to identify genetic variants that regulate visceral pain in people with visceral pain disorders, or in individuals who continue to experience pain despite remission or treatment. While we aim to conduct hypothesis-generating research, the genetic analysis will focus on identifying potential variants with moderate to strong effects, acknowledging that smaller effect sizes may require larger cohorts for reliable detection. The genetic approaches used have been proven effective in cohorts as small as 30–200 individuals with pain phenotypes [18]. However, we acknowledge that the requirement for ≥30 exomes per visceral disease pain phenotype may limit statistical power to detect genetic variants with modest effect sizes. Our analysis will explicitly report effect sizes, confidence intervals, and limitations related to sample size constraints in all genetic findings. Where modest effect sizes are detected, these will be flagged as requiring replication in larger cohorts. Findings will be reported in line with STREGA and STROBE guidelines for genetic association studies.

We note the following:

At least 30 exomes are required per visceral disease pain phenotype to yield statistically valid results, in terms of the power to detect significant associations between genetic variants and pain phenotypes.DNA extraction failure rates are expected to be no more than 5% from blood samples and negligible from serum samples.

For this study, the following visceral pain phenotypes will be analysed, representing a broad spectrum of pain associated with visceral organ pathology:

1Polycystic kidney disease2Inflammatory bowel disease3Post-vaginal mesh surgery4Chronic pancreatitis5Endometriosis6Painful bladder syndrome

Additionally, similar analyses will be conducted in the Lack of Visceral Pain cohort, where the severity of visceral disease does not correspond to expected levels of pain. This group will allow us to explore potential genetic mechanisms underlying discordant pain experiences. The following phenotypes will be included in this cohort:

1Polycystic kidney disease2Inflammatory bowel disease3Chronic pancreatitis4Chronic pain syndromes (e.g., fibromyalgia, Complex Regional Pain Syndrome, migraine)5Cases of painlessness during percutaneous visceral organ procedures (e.g., biopsies)6Overactive bladder syndrome

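### Table 1's bio-sampling row requires pain, so pain-free Lack of Visceral Pain patients without a pain condition diagnosis cannot give the samples planned from that cohort

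*Protocol article*

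**What the plan says.** Table 1 is captioned "Inclusion and Exclusion Criteria for the Extreme Visceral Pain and Lack of Visceral Pain cohorts", so each row applies to both patient groups. Three rows matter here.

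- **App row:** "Pain, or lack of pain, associated with one or more of the specified visceral diseases or chronic pain conditions", as diagnosed by an NHS expert.
- **Wearable row:** takes over the app row's criteria by reference.
- **Bio-sampling row:** states its own criterion, "Pain associated with one or more of specified visceral diseases or pain condition diagnosis by an NHS medical professional". It adds a second one, "Meet further clinical criteria for genetic sampling and analysis (see Supplementary Information"), and lists failure to meet the inclusion criteria as an exclusion.

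Elsewhere the article expects samples from both groups. The Fig 1 legend says "Extreme Visceral Pain and Lack of Visceral Pain cohorts provide biological samples". The Bio-sampling section says "Participants from Extreme Visceral Pain and Lack of Visceral Pain cohorts will be asked to provide various samples". After listing the pain phenotypes for exome work, the Key exploratory endpoint section says that "similar analyses will be conducted in the Lack of Visceral Pain cohort". It names six phenotypes for that cohort, one of them patients who felt no pain during a needle procedure on an organ.

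**The concern.** The Lack of Visceral Pain cohort exists to study people whose disease should hurt but does so little or not at all. Those with no pain are the far end of that phenotype and the most informative donors for a search for variants that reduce pain. The bio-sampling row, taken literally, is the one place in the article that shuts them out.

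The participant recruitment section says clinical teams identify patients against Table 1, so the row is a working rule and not a loose summary. If it is followed, the discordant-pain genetics and the comparison of high-pain with little-or-no-pain patients lose some or all of their pain-free donors. If it is ignored, samples are taken from people who are ineligible under the published criteria. Either outcome is awkward to report.

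**Working it through.** The plan has no figure to reproduce here; the check is a comparison of texts.

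**Step 1: does the table itself separate pain from its absence?** Yes. The app row names both states and the bio-sampling row names only the first. The wearable row inherits the app criteria but the bio-sampling row does not, so the wider wording is not carried across.

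**Step 2: how can the row be parsed?** There are two readings.
- (a) Disease-associated pain, *or* a diagnosed pain condition.
- (b) Pain associated with *either* a visceral disease *or* a diagnosed pain condition.

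**Step 3: apply both readings to the kinds of patient in the Lack cohort.**
- *Active visceral disease, no pain, no pain condition diagnosis:* passes the app row; fails bio-sampling under (a) and (b).
- *Low-level disease pain:* passes under both. The Remote mobile app section says that a score under 4 need not mean absence of pain.
- *Chronic pain syndrome diagnosis (one of the six Lack phenotypes):* passes under (a); passes under (b) if the syndrome is painful.
- *Painless during a procedure:* depends on whether the disease hurts at other times. The row asks about disease pain, not procedural pain.
- *Intermittent disease pain but diary scores of 0:* can pass, because the row sets no score threshold.

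Only the first group is barred on every reading.

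**Step 4: can the supplement rescue the row?** The supplementary genetic criteria are not shown. Table 1 lists them as an additional requirement, so as written they narrow eligibility further and do not waive the pain requirement.

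**Step 5: scale of the analysis exposed.** The Key exploratory endpoint section asks for at least 30 exomes per visceral disease pain phenotype and allows up to 5% DNA extraction failure from blood. *Assuming* the same minimum applies to the Lack phenotypes, which the article implies but does not state:
- exomes: 6 × 30 = 180
- participants to sample per phenotype: 30 / 0.95 = 31.6, rounded up to 32
- participants to sample in all: 6 × 32 = 192

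This is the size of the donor pool that the analysis would draw on. It is not the number excluded. That number would need the pain-free share of the cohort, which the article does not give.

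**The case against.** The best defence is that the intent is plain. The table is captioned for both cohorts, and two other places say both give samples, so some words were probably dropped in drafting and sites would sample anyway. That is likely true of the cause, but it does not remove the conflict, because the article makes Table 1 the screening standard.

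The defence is stronger on extent. A reader might infer four things that the documents do not support:

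- *That the whole Lack cohort is barred.* The Methods and analysis section defines it by low or no pain, so members with mild disease pain meet the row, and the pain condition wording offers another way in.
- *That the whole procedural-painlessness phenotype is lost.* Feeling nothing during a biopsy does not show that the disease itself is painless.
- *That the sampled group is cut to diary scores of 1 to 3.* The row refers to disease-associated pain or a diagnosis, not to a current score.
- *That patients have been turned away.* Nothing in the article shows a refusal.

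Two further limits stand. The need for Lack samples is explicit for genetics. For autoantibodies it is inferred from the Secondary endpoint analyses section, which describes them across the cohorts and specifies no test between the Extreme and Lack groups. And the full protocol and supplement, which are not shown, may already be worded correctly.

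**Conclusion.** The contradiction is real but narrower than it first looks. As published, the bio-sampling row makes pain-free Lack of Visceral Pain patients without a pain condition diagnosis ineligible for samples that the Fig 1 legend, the Bio-sampling section and the Key exploratory endpoint section all expect from that cohort.

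The number affected cannot be derived. The consequence is confined to the genetic and other biosample analyses, which the article calls exploratory. The primary wearable regression draws on the Extreme Pain cohort and is untouched.

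The conclusion assumes that the row is applied literally and that the unseen supplementary criteria add to it, as the table presents them. It is worth correcting now: the Study status section reports recruitment as ongoing, with completion anticipated by 30 June 2026.

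**What to change.** Reconcile the bio-sampling row of Table 1 with the Fig 1 legend, the Bio-sampling section and the Key exploratory endpoint section. The simplest way is to open the criterion as the app row does, "Pain, or lack of pain, associated with one or more of the specified visceral diseases", followed by the pain conditions and the requirement for an NHS diagnosis.

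Then confirm that the full protocol and the supplementary genetic sampling criteria use the same wording. If only the article is affected, a correction to the article is enough; if the full protocol has the same line, it needs a short amendment.

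The cost is one line of text and a cross-check of two documents. No procedure is added, since sampling of this cohort is already planned.

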### Participation procedure

The complete flow of participation is described in Fig 2, from recruitment to end of study. Participation in the study is entirely voluntary, and participants may withdraw at any time for any reason or be withdrawn by the Investigator. Data collected before withdrawal will be retained, identified only by Study ID, and will be fully anonymized. Choosing not to participate or withdrawing from the study will not affect the healthcare access or legal rights of participants. Participants attending onsite research visits will be reimbursed up to £15 per visit, in accordance with local site policies.

**Fig 2 pone.0350169.g002:**
[figure not shown]
Participant Recruitment and Cohort Assignment Flow Diagram. Flowchart depicts screening, eligibility assessment, randomisation, and cohort assignment processes. NHS patient referrals and healthy volunteer recruitment pathways lead to initial screening using inclusion/exclusion criteria (Table 1). A six-week *ADVANTAGE Diary* remote mobile app phase determines cohort assignment: Extreme Visceral Pain (pain ≥4 on two occasions ≥1 week apart), Lack of Visceral Pain (pain <4 throughout), Healthy Controls (baseline only). Subsequent baseline/follow-up visits include optional wearable sub-study and bio-sampling as per eligibility. Decision points and participant progression shown chronologically.

### Remote mobile app study

If the participant consents, they will be provided with a link to download the *ADVANTAGE Diary* remote mobile app. The app is hosted on a UK-based server that complies with General Data Protection Regulations (GDPR). Data access is protected using HTTPS and OpenID Connect 1.0 standards, with authentication managed through industry-standard OAuth 2.0 protocols. *ADVANTAGE Diary* is designed to meet Data Security Standard 4, equivalent to NHS hosting requirements. Participants will give informed e-consent via *ADVANTAGE Diary*, which will collect necessary information, such as their email address and a unique identifier generated by the app.

### On-site study visit

Informed consent will be obtained either electronically or on paper at the start of the on-site visit. Electronic or scanned paper consent forms will be securely stored in the University of Cambridge Clinical School Data Safe Haven. Each participant will be assigned a unique Study ID, which will also be securely stored. Explicit consent will be sought for (a) genetic analyses, (b) planned use of serum for *in vitro* or *in vivo* (mouse) studies, and (c) storage of serum and other samples (e.g., urine, vaginal swabs, faeces) for use in future ethically approved research. Individualized results from the analysis of these samples will not be disclosed to participants or their clinicians.

Only participants who have completed the mobile app sub-study are eligible for the wearable sub-study.

### Baseline on site visit assessments

#### Remote mobile app.

The *ADVANTAGE Diary* remote mobile app will be used to intermittently track pain experiences [20]. Participants will be asked to download the app from major platforms (e.g., App Store, Play Store) and will be registered by the study team with a unique study identifier. Over a period of up to 6 weeks, individuals will use the app to rate their visceral pain by responding to the prompt, “Please rate the severity of your pain right now,” on an 11-point Likert scale. The scale ranges from 0, representing no pain, to 10, representing the worst pain imaginable. This will specifically relate to their visceral pain. Individuals are encouraged to record their pain daily, and during painful “flares” as needed. The *ADVANTAGE Diary* remote mobile app will send reminders, no more than once daily, for these ratings. During this 6-week period, participants reporting a pain score of 4 or higher on two separate occasions at least one week apart will be placed in the Extreme Pain cohort, while those with scores below 4 will join the Lack of Visceral Pain cohort. This distinction is made to simplify cohort classification and study procedures. It does not imply that participants with scores below 4 are pain-free, nor that a score of 4 or 5 necessarily represents extreme pain; rather, it provides a practical framework for grouping participants based on pain intensity levels.

In exceptional cases where individuals face difficulties accessing the app due to IT literacy or lack of smartphone access, a telephone screening will be arranged. The study team will ask participants to rate their pain over the phone, using the same 0–10 scale.

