### Aims and endpoints

The overarching aim of this study is to deepen our understanding of chronic visceral pain by identifying and evaluating the genetic, molecular, and physiological mechanisms that contribute to this condition. We will examine these mechanisms across different participant groups, including those with extreme visceral pain, those with a lack of expected pain despite visceral disease, and healthy controls.

Our **primary objective** is to look for physiological markers (such as changes in movement, heart rate, and postural patterns) that predict or associate with visceral pain flares by examining data from wearable sensors. This will provide objective, real-time insights into how visceral pain affects day-to-day activities, and will be tested using a pre-specified statistical model and is central to the confirmatory aspect of the study.

In addition, we will undertake a series of **secondary/exploratory objectives**, which include the following key areas of investigation:

1**Genetic insights:** We aim to identify and characterize the genetic factors that underlie chronic visceral pain in specific participant cohorts, which include individuals with conditions like polycystic kidney disease, inflammatory bowel disease, chronic pancreatitis, endometriosis, and painful bladder syndrome.2**Spatial and temporal pain mapping:** We will create detailed maps of where and when individuals experience visceral pain. This includes analysing the frequency and intensity of pain reported by participants using a remote mobile app and wearable sensors that track body movement, posture, heart rate, and breathing.3**Biological sample analysis:** We will collect a variety of biological samples—blood, urine, low vaginal swabs, and faeces—from participants to explore pain mediators and modulators. This will include testing human serum in passive transfer experiments using mice to better understand the role of autoantibodies and other pain-related factors [19].4**Comparing pain groups:** We will compare participants with high levels of visceral pain, regardless of disease activity, to those with little or no visceral pain despite having active disease. These groups will be contrasted with healthy control subjects to uncover key differences in pain experience and physiology.

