### Methods and analysis

This study is designed to explore chronic visceral pain through the recruitment and analysis of three distinct cohorts: **Extreme Visceral Pain** (individuals with high pain despite low disease activity), **Lack of Visceral Pain** (those with low or no visceral pain despite high disease activity), and **Healthy Controls** (from volunteers). This multi-faceted approach will allow us to examine the complex relationships between pain, disease activity, and biological markers, providing new insights into the mechanisms of chronic visceral pain. Each cohort will undergo tailored assessments, with the primary goal of identifying functional pathways that differentiate pain experiences across these diverse groups.

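### Patient cohorts are defined by pain discordant with disease activity but assigned on pain ratings alone, by a rule that leaves some patients in neither cohort

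*Protocol article*

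**What the plan says.** Under Methods and analysis, the Extreme Visceral Pain cohort is "individuals with high pain despite low disease activity" and the Lack of Visceral Pain cohort is "those with low or no visceral pain despite high disease activity". Participant recruitment and the Fig 1 caption say the same in other words. Objective 4 under Aims and endpoints instead describes the high-pain side of the comparison as "participants with high levels of visceral pain, regardless of disease activity".

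The operative rule is under Baseline on site visit assessments, Remote mobile app. Its first half sets entry to the high-pain group: "pain score of 4 or higher on two separate occasions at least one week apart will be placed in the Extreme Pain cohort". Its second half deals with the low-pain group and reads: "while those with scores below 4 will join the Lack of Visceral Pain cohort". The Fig 2 caption says that the six-week "remote mobile app phase determines cohort assignment" and words the second group as "Lack of Visceral Pain (pain <4 throughout".

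Ratings are collected for up to six weeks. Daily entry is encouraged, extra entries may be made during flares, and no minimum number is given. Disease activity scores are recorded at the Structured clinical interview but do not enter the rule. Table 1 sets no activity threshold for the app or wearable sub-studies.

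**The concern.** Three statements of who belongs in the high-pain cohort do not agree: low activity, any activity, and activity not considered. Only the last is put into operation. Key exploratory endpoint then treats the Lack cohort as people whose disease severity does not match their pain, and looks there for variants that act independently of severity. A label built without severity cannot carry that interpretation.

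The rule is also written as two categories that do not cover all rating patterns. And because it needs two qualifying events a week apart, with no required number of ratings, two patients with the same pain can receive different labels because one uses the diary more.

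**Working it through.** **Definition against assignment.** The four combinations of pain and activity, taking the written rule as it stands:

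| Pain ratings | Disease activity | Cohort by definition (Methods and analysis) | Cohort by rule (Remote mobile app, Fig 2) |
|---|---|---|---|
| High | Low | Extreme | Extreme |
| High | High | neither | Extreme |
| Low | High | Lack | Lack |
| Low | Low | neither | Lack |

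The two concordant rows are labelled as if they were discordant. Under objective 4 the second row would belong in the high-pain group, but the fourth row fits no description in the document.

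**Coverage.** Extreme needs two ratings of 4 or more at least 7 days apart. Lack, by Fig 2, needs every rating below 4. A patient with exactly one rating of 4 or more, or with several all less than 7 days apart (a single flare), meets neither. The Remote mobile app wording on its own might be read as everyone else joins Lack; Fig 2 rules that reading out.

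**Dependence on rating frequency.** The protocol gives no misclassification figure to reproduce. Inputs from the document: threshold 4, spacing 7 days, window up to 42 days. Assumptions, not in the document: each rating is 4 or more with probability q, independently, and the rating schedules are as listed.

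- Lack, m ratings: (1−q)^m.
- Unassigned, weekly rating (m = 6, any two ratings at least 7 days apart): 6q(1−q)^5.
- Unassigned, daily rating (m = 42; first high rating on day i and none from day i+7 on, summed over i): 36q(1−q)^35 + (1−q)^36 − (1−q)^42.
- Extreme: the remainder.

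At q = 0.10:
- daily: unassigned 0.0901 + 0.0225 − 0.0120 = 0.101; Lack 0.012; Extreme 0.887.
- weekly: unassigned 6 × 0.10 × 0.9^5 = 0.354; Lack 0.9^6 = 0.531; Extreme 0.114.

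At q = 0.05:
- daily: unassigned 0.2990 + 0.1578 − 0.1160 = 0.341; Lack 0.116; Extreme 0.543.
- weekly: unassigned 6 × 0.05 × 0.95^5 = 0.232; Lack 0.735; Extreme 0.033.

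Simulation agrees with these and supplies the schedules without a simple formula:

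| q | Schedule | Extreme | Lack | Unassigned |
|---|---|---|---|---|
| 0.05 | daily, 42 days | 54% | 12% | 34% |
| 0.05 | twice weekly | 10% | 54% | 36% |
| 0.05 | weekly | 3% | 74% | 23% |
| 0.10 | daily, 42 days | 89% | 1% | 10% |
| 0.10 | twice weekly | 30% | 28% | 41% |
| 0.10 | weekly | 11% | 53% | 35% |
| 0.10 | daily, first 14 days only | 19% | 23% | 58% |
| 0.20 | daily, 42 days | 99.7% | 0% | 0.3% |
| 0.20 | weekly | 34% | 26% | 39% |

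Over q = 0.02 to 0.30 the unassigned share runs from 41% down to about 0% with daily rating, and between 11% and 39% with weekly rating.

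**Clustered flares.** Independence is a strong assumption for flares. With a two-state chain in which the chance of a high rating is q + r(1−q) after a high day and q(1−r) after a low day, q = 0.10 gives, for daily / twice weekly / weekly rating:

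- r = 0.5: Extreme 57 to 58% / 27% / 12%; unassigned 31% / 41% / 35%.
- r = 0.8: Extreme 29% / 21% / 14%; unassigned 32% / 30% / 26%.

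The effect of rating frequency on the Extreme label shrinks but keeps its direction, and the gap stays.

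**The case against.** The best defence is that the protocol discloses the rule as a simplification for grouping by pain intensity, and says that a score of 4 or 5 need not be extreme pain. That answers a complaint about the cut-off. It does not mention disease activity, so the conflict with Methods and analysis remains.

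Four further objections stand and limit the point.

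- A reader might infer that the genetic and antibody results are confounded by the cohort label. The document does not support this. The allele-frequency tests compare exomes with the general population, and the autoantibody models use pain severity, adjusted for age, gender and disease type. A mixed cohort can dilute the phenotype and weaken the discordance reading, but cohort is not the stated exposure in either.
- Table 1 requires bio-sampling participants to meet further genetic sampling criteria in the supplement, and Structured clinical interview mentions those criteria next to the activity scores. They may already select on activity. They are not cited for cohort assignment or for the wearable sub-study.
- A reader might infer that the primary analysis is compromised. It is one regression in Extreme-cohort wearable users, with no cohort comparison, and wearable entry requires adherence to the app procedure, although adherence is not quantified.
- The percentages depend on an assumed q. For patients who rate daily and are often in pain the gap nearly vanishes if ratings are independent.

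A reader might also infer that patients screened by telephone can never be Extreme. The text says only "The study team will ask participants to rate their pain over the phone" and gives no number of calls. One call could not meet the two-occasion rule, but a single call is an assumption, and the route is for exceptional cases.

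**Conclusion.** The point holds in limited form. The definitions conflict with each other and with the assignment rule. Followed as written, the rule labels concordant patients as discordant. The comparison in objective 4 and the reading of the Lack cohort as discordant are therefore not supported by the label, unless the unseen sampling criteria restrict the bio-samples by activity.

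The non-exhaustive rule is a matter of text and needs no assumption. Its size does: under independent ratings with 5 to 10% at 4 or more, 10 to 34% of daily raters and 23 to 35% of weekly raters are unassigned, falling to near 0% for daily raters at 20% or more. No rate of high ratings and no actual diary frequency is given, so these figures show sensitivity and do not forecast the trial.

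This should be fixed. It is not a condition for the primary result, because the affected contrasts are declared exploratory and the primary regression does not compare cohorts.

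**What to change.** 1. Reconcile Aims and endpoints, Methods and analysis, Participant recruitment, the Fig 1 and Fig 2 captions and the Remote mobile app section, so that one definition of each cohort applies throughout.
2. For any analysis that claims discordance, form the analysis groups with the disease-activity scores already collected at the interview, where the disease has such a score. Where it has none, describe the groups as high-pain and low-pain only. If the supplementary sampling criteria already do this, cite them in the cohort definition.
3. Name an intermediate group for patients who meet neither rule, and state which analyses they enter.
4. Report the number of ratings per patient by cohort, and add a sensitivity analysis restricted to patients with adequate diary completion, with adequate defined before the data are analysed.

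The pain threshold and the wearable regression population need not change. A fixed share-of-days criterion or a scheduled-ratings-only rule would be a preference, and the second assumes that scheduled and flare entries can be told apart, which the text does not establish.

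The cost is protocol wording and some derivation work; the protocol reports that no analysis has yet been done. The contrast groups become smaller, and activity scores exist only for those who attended the on-site interview.
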